### 5.2.2 Participant eligibility

We chose to focus our study population on pwPMS, as evidence suggests that patients may be less likely to engage in ACP if they perceive themselves as 'too healthy' [Schickedanz 2009].

PwPMS (in- or outpatients) will be included if they:

- Are ≥18 years of age;
- Were diagnosed with primary or secondary PMS [Lublin 1996] from one or more years before inclusion;
- Are able to communicate in Italian;
- Gave written consent;
- Have one or more of the following conditions that would make ACP relevant:
  - Express desire for ACP;
  - Raise questions about their future;
  - Talk about hastening death or medically assisted suicide;
  - High risk for death within two years using the 'Surprise Question' [Downar 2017];
  - High risk for development of severe cognitive compromise/dementia within two years;
  - High risk for development of impairments preventing communication within two years;
  - Significant suffering (e.g. uncontrolled physical symptoms, psychosocial or existential issues).

PwPMS will be excluded if they have one or more of the following:

- Severe cognitive compromise (MMSE < 19) or impairments preventing communication;
- Psychosis or other serious psychiatric conditions;
- Advance care plan document completed.

### **5.2.3 Recruitment**

PwPMS are recruited prospectively by the ACP-trained physicians involved in their care, when the potentially eligible pwPMS attends the center for an outpatient visit or hospitalization. PwPMS who show interest in participating receive full verbal and written information about the study purpose and procedures.

### **5.2.4 Baseline assessment (T0)**

The ACP-trained physician makes an appointment with pwPMS who provided initial verbal consent to participate in the study, and checks all eligibility criteria.

A written, signed informed consent is obtained, according to the Declaration of Helsinki and to the Good Clinical Practice (GCP) Guidelines of the EU. The informed consent is kept on file by the study personnel, and is available for inspection by regulatory authorities or authorized persons.

Then, the physician gives the pwPMS the credentials to the trial platform, so that the pwPMS completes the baseline set of questionnaires/instruments (the total assessment will last about 40 minutes). In the event the pwPMS has difficulties in using the trial platform, a phone interview is scheduled within a week with an independent, trained interviewer who will administer the questionnaires/instruments.

The ACP conversation is scheduled at the center, within three weeks. The pwPMS is invited to involve his/her SO (family member, relative, or friend, who is next of kin or is key decision maker as designated by the pwPMS and with whom the pwPMS shares his/her life). If the pwPMS agrees on involving his SO, a SO's telephone number is asked for so that the SO can be contacted by a study researcher to confirm eligibility, explain the study and obtain verbal consent. Consenting SOs receive credentials to access the trial platform and complete the baseline set of questionnaires (completion time about 15 minutes). If the SO has difficulty in using the trial platform, a phone interview is scheduled within a week with an independent, trained interviewer who will administer the questionnaires.

Finally, the physician completes the CRF via the trial platform.

Each center will collect information on the number of pwPMS and SOs approached, screened, and eligible prior to enrollment, with reasons for non-enrolment.

#### **5.2.5 ACP conversation**

The ACP conversation involves the pwPMS, the ACP-trained physician involved in his/her care and, when applicable, the SO. In addition, if the pwPMS agrees, the non-physician ACP-trained HP at the center will participate.

*The first conversation* takes place in a dedicated room at the center, and is audio-recorded. A one-hour slot is reserved for the conversation, and in the case a SO participates it is envisaged that there will be a session closed to the SO, followed by an open session.

About one week before the scheduled first ACP conversation, reminder emails (or phone calls) are sent to pwPMS/SOs. At the end of the first ACP conversation, the physician invites the pwPMS (when applicable the SO) to complete the T1 follow-up assessment within one week. The physician completes the QOC-Doc immediately after the ACP conversation terminates.

#### **5.2.6 Follow-up assessments (T1, T2)**

The pwPMS completes the questionnaires by one week (T1, assessment time of about 20 minutes) and six months after (T2, assessment time of about 30 minutes) the ACP conversation. The SO completes the questionnaires/instruments (T1, assessment time of about 20 minutes). All the questionnaires are self-completed using the trial platform, except the QOC and the QOC-SO. These questionnaires, originally envisaged as being self-completed, resulted emotionally taxing in the cognitive debriefing sub-study (section 5.3.9). Consequently, an independent, trained interviewer will administer the QOC and the QOC-SO in a phone interview. Before the interview, the interviewer will be notified whether, in the first ACP conversation, EOL care was discussed, or not. If not discussed, the nine QOC/QOC-SO items on communication about EOL care (section 5.3.4) will be skipped (adaptive administration).

In the event the pwPMS/SO have difficulties in using the trial platform, the independent interviewer will administer all the questionnaires/instruments in scheduled telephone interviews.

About one week before the T2 assessment, reminder emails (or phone calls) are sent to pwPMS.

The physician completes the questionnaire (T1, QOC-Doc) and the CRF using the trial platform.

He/she records on the platform the date, duration, participants, and mode (face to face, teleconference or on the telephone) of subsequent ACP conversations that occur during follow-up.

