| QOC-Doc | Physician      | Communication quality (physician's skills) | –              | –            | T1       |
| QOC-SO  | SO             | Communication quality (physician's skills) | –              | –            | T1       |
| ZBI     | SO             | Caregiver burden                           | Hérbert 2000   | Chattat 2010 | T0/T1/T2 |

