#### **5.3.4 Quality of the ACP conversation**

*OPTION scale* - Structured observations of audio recorded ACP conversations will be assessed using the OPTION scale. The ACP conversation will be unobtrusively audio-taped and transcribed verbatim; subsequently it will be rated by a specially trained third observer using the Observing Patient Involvement in Shared Decision Making (OPTION) scale. OPTION (<http://www.glynelwyn.com/observer-option-instrument.html>) is an observer-based scale that evaluates the behavior of the physician in terms of patient involvement in decision-making [Elwyn 2005]. It consists of 12 items, each rated on a five-point Likert scale ranging from 0 (behavior not observed) to 4 (behavior observed to high standard). A total score (range 0–48) is obtained by adding the scores of each item. OPTION has been validated in seven languages, including Italian [Goss 2007].

*QOC, QOC-SO and QOC-Doc* - After the ACP conversation, pwPMS will complete the Quality of Communication Questionnaire (QOC) [Engelberg 2006]; SOs will complete the SO version, and physicians the physician version (last two items) of the QOC. Developed from qualitative studies with patients, families, and clinicians, the QOC consists of 19 items measuring general communication (ten items) and communication about EOL care (nine items), each rated on a scale from 0 ('very worst I can imagine'/'not at all') to 10 ('very best I can imagine'/'extremely'), or identified as something the clinician did not do. The 0/10 ratings are recoded to 1/11, with 0 imputed for 'did not do' (<http://depts.washington.edu/eolcare/products/instruments/>). A SO's version of the inventory (QOC-SO), and a physician's version (QOC-Doc, made of the last two items only) will be also devised for this study.

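### The QOC-SO end-of-life items are routed on the whole first conversation, although part of it is envisaged as closed to the significant other

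*Protocol*

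**What the plan says.** Section 5.2.5 describes the first ACP conversation as a one-hour slot. On the SO's part in it, the section says: "in the case a SO participates it is envisaged that there will be a session closed to the SO, followed by an open session". Both sessions belong to the same first conversation.

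Section 5.2.6 has a trained independent interviewer administer the QOC and QOC-SO by telephone at T1, because the questionnaires "resulted emotionally taxing in the cognitive debriefing sub-study (section 5.3.9"). The routing rule is: "Before the interview, the interviewer will be notified whether, in the first ACP conversation, EOL care was discussed, or not". It continues: "If not discussed, the nine QOC/QOC-SO items on communication about EOL care (section 5.3.4) will be skipped (adaptive administration").

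Section 5.3.4 gives the structure and scoring: "the QOC consists of 19 items measuring general communication (ten items) and communication about EOL care (nine items"). Each item is rated 0 to 10 or marked as something the clinician did not do, and "The 0/10 ratings are recoded to 1/11, with 0 imputed for 'did not do"'. The SO form is new to the trial: "A SO's version of the inventory (QOC-SO), and a physician's version (QOC-Doc, made of the last two items only) will be also devised for this".

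Table 2 in section 5.3 lists the QOC-SO as a secondary measure, rated by the SO at T1, with the construct "Communication quality (physician's skills").

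**The concern.** The patient is present for all of the first conversation; the SO is expected to be present for only part of it. Section 5.2.6 nevertheless describes a single filter, set at the level of the conversation, and applies it to both questionnaires. That is right for the patient but can be wrong for the SO.

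Three things are at stake:

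- **Validity of the QOC-SO EOL items.** The Summary names quality of communication about EOL care as a secondary efficacy outcome, and Table 2 treats the QOC-SO as a measure of physician skill. A zero that arises because the SO was outside the room says nothing about skill.
- **The purpose of the adaptive rule.** It was introduced because the questionnaires were taxing, so that people are spared EOL items when EOL care was not discussed. An SO for whom it was discussed only behind a closed door gets all nine.
- **A signal to the SO.** An SO who knows or guesses that the items are conditional could infer that EOL care was raised in private.

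**Working it through.** **1. Inputs from the protocol.** One notice per first conversation, applied to both the QOC and the QOC-SO (5.2.6). A closed session followed by an open one when an SO takes part (5.2.5). Ten general plus nine EOL items, 10 + 9 = 19, which agrees with the stated total (5.3.4). Ratings recoded to 1–11, with 0 for 'did not do' (5.3.4). The protocol gives no figure for the share of conversations in which EOL care is confined to the closed session, so there is no stated number to reproduce.

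**2. Routing under the rule as written.** With two sessions there are four possibilities:

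| EOL in closed session | EOL in open session | Notice | Patient's nine items | SO's nine items | Suitable for the SO? |
|---|---|---|---|---|---|
| No | No | No | skipped | skipped | yes |
| No | Yes | Yes | asked | asked | yes |
| Yes | Yes | Yes | asked | asked | yes |
| Yes | No | Yes | asked | asked | **no** |

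The patient is routed correctly in every row. The SO is misrouted in the last row only.

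**3. What the misrouted SO can answer.** Section 5.3.4 names two kinds of response: a rating, or 'did not do'. A rating would be a guess or hearsay, with an error of unknown direction. 'Did not do' scores 0, one point below the worst actual rating, which is recoded to 1. No answer for not having been present is named.

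**4. Illustrative size.** Let *m* be the mean recoded item score among SOs who heard EOL talk, and *f* the share of SOs asked the EOL items who heard none and answer 'did not do' throughout. The observed mean is *m*(1 − *f*), a shift of −*f* × *m*. Both *m* and *f* are assumptions.

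| *f* | *m* = 6 | *m* = 8 | *m* = 10 |
|---|---|---|---|
| 10% | 5.4 (−0.6) | 7.2 (−0.8) | 9.0 (−1.0) |
| 20% | 4.8 (−1.2) | 6.4 (−1.6) | 8.0 (−2.0) |
| 30% | 4.2 (−1.8) | 5.6 (−2.4) | 7.0 (−3.0) |

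If 20 SOs were rated (also an assumption), one such SO would move a mean of 8 by 8 / 20 = 0.4.

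**5. Could it be repaired afterwards?** Section 5.2.6 has the physician record participants for later conversations, but names no session-level record of EOL discussion for the first. The first conversation is audio-recorded, so the sessions could be coded retrospectively. That would identify affected SOs but would not undo the questions already put to them.

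**The case against.** The strongest reply is that this is an edge case in operational detail. The closed session is only envisaged; EOL care may usually be taken up again in the open session; a trained interviewer can use judgement; and answer codes for a new form could sit in a manual or CRF. Nor does the protocol say outright that the patient's interviewer and the SO's interviewer receive the same notice, though that is the natural reading. This limits the likely size and the confidence in it. It does not remove the point, because the protocol itself fixes the routing rule and, followed as written, the rule misroutes the SO in the last row of the table.

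The QOC-SO wording is not shown. It may ask about talk with the SO or with the patient, and it may offer further answers. The scoring consequence therefore rests on the response options that section 5.3.4 describes for the QOC.

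A reader might infer more than the documents support:

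- *That SOs who never attended will be given the QOC-SO.* Section 5.2.5 has the physician invite the SO to T1 at the end of the conversation, where applicable. This largely covers attendance.
- *That the SO would learn what the patient said in private.* At most the SO could infer that EOL care came up, and only if aware that the items are conditional. The protocol does not say SOs are told this, and it states no purpose for the closed session.
- *That a planned patient–SO comparison would be distorted.* Section 5.5.2 specifies no agreement analysis of QOC against QOC-SO. The congruence outcome in section 5.3 concerns treatment preferences.

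**Conclusion.** The point holds in limited form. Section 5.2.6 ties the QOC-SO EOL items to the whole first conversation, section 5.2.5 envisages the SO missing part of it, and no other section reconciles the two. Where EOL care is raised only in the closed session, the SO is asked nine unsuitable items, and the one non-rating answer named turns absence into the lowest score.

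The effect falls on one secondary measure, taken once, in a single-arm pilot. Its size cannot be established from the protocol. The fall from 8 to between 7.2 and 5.6 assumes an item mean of 8, a misrouted share of 10% to 30%, and 'did not do' on every item by every affected SO. The primary endpoint, the sample size and the numerical criteria in section 6 for proceeding to a phase III trial do not use the QOC-SO EOL score. It is worth correcting because it is a data-collection rule that must be right before the interviews take place.

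**What to change.** In section 5.2.6:

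- Have the physician record two items on the platform when completing the QOC-Doc: EOL care discussed in the closed session (yes/no), and in the open session (yes/no).
- Route the patient's nine EOL items on a yes for either session.
- Route the SO's nine EOL items only on EOL discussion in the SO's presence, and give the SO's interviewer only that flag. This also deals with the signalling risk.
- In section 5.3.4, code the skipped QOC-SO items as not applicable, distinct from 'did not do' = 0.

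The cost is two tick boxes on a platform the physician already uses, a sentence in 5.2.6 and a scoring note in 5.3.4. The downside is that slightly fewer SOs contribute EOL ratings; those lost are the ones who heard nothing to rate.

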### 5.2.7 Withdraw

Participants (pwPMS, SOs) will be free to withdraw from the study at any time, without giving reasons and with no risk of prejudicing future care. Study personnel will make every effort to obtain, and record, information about the drop out reasons.

## 5.3 Outcome Measures

A range of measures will be collected to capture the full process of ACP and whether the *ConCure-SM* intervention has any effect on completion of an advance care plan document (primary outcome measure), congruence in treatment preferences between pwPMS and their carers, quality of patient-clinician communication, and caregiver burden. In addition, since a study-related increase in emotional burden can't be excluded, serious adverse events (SAE: admission to psychiatric ward, suicide attempt, death) will be monitored by the independent Data and Safety Monitoring Committee (DSMC). Mood symptoms will be assessed at baseline and during follow-up.

We are aware that long-term outcomes (chiefly the concordance between preferred and received EOL care and treatments) are warranted. However, the MS trajectory further challenges the collection of this outcome in the typical timeframe of a clinical trial. The assessment of this outcome in pwPMS could be feasible by focusing on the late stages of the disease only. In line with the principles of ACP, we agreed not to narrow the inclusion criteria deserving this relevant outcome to future studies.

We will use the published Italian version of the following inventories: CPS [Giordano 2008], HADS [Costantini 1999], OPTION [Goss 2007], MSQOL-29 [Rosato 2016], ZBI [Chattat 2010].

The 4-item ACP-E and the QOC inventories will be translated and culturally adapted from source language (section 5.3.8).

**Table 2.** Secondary outcome measures of the trial (in alphabetical order)

| Scale name   | Assessor | Construct          | Author       | Italian version | Timing   |
|--------------|----------|--------------------|--------------|-----------------|----------|
| 4-item ACP-E | Patient  | ACP engagement     | Sudore 2017  | –               | T0/T1/T2 |
| eCPS         | Patient  | Role preferences   | Degner 1997  | Solari 2013     | T0       |
| HADS         | Patient  | Mood symptoms      | Zigmond 1983 | Costantini 1999 | T0/T1/T2 |
| MSQOL-29     | Patient  | Health-related QOL | Rosato 2016  | Rosato 2016     | T0/T2    |

| OPTION  | Third observer | SDM (physician's skills)                   | Elwyn 2005     | Goss 2007    | –        |
|---------|----------------|--------------------------------------------|----------------|--------------|----------|
| QOC     | Patient        | Communication quality (physician's skills) | Engelberg 2006 | –            | T1       |
| QOC-Doc | Physician      | Communication quality (physician's skills) | –              | –            | T1       |
| QOC-SO  | SO             | Communication quality (physician's skills) | –              | –            | T1       |
| ZBI     | SO             | Caregiver burden                           | Hérbert 2000   | Chattat 2010 | T0/T1/T2 |

### 5.3.1 ACP completion

Standard ACP is measured by the completion of advance care plan in the patient medical record. We will assess occurrence and signature date of advance care plan document.

### 5.3.2 ACP engagement

The ACP process will be assessed using the 4-item ACP engagement questionnaire. Originally developed and validated to measure the complex behavior of ACP, it consists of different versions (i.e. 55-item, 34-item, 9-item, 4-item). In this study, we will use the 4-item version which focuses on the readiness behavior change construct within the quality of life ACP domain. Responses are on a 5-point Likert scale (1 “I have never thought about it”; 2 “I have thought about it, but I am not ready to do it”; 3 “I am thinking about doing it in the next 6 months”; 4 “I am definitely planning to do it in the next 30 days”; 5 “I have already done it”) [Sudore 2017].

### 5.3.3 Treatment preferences

*CPS* - The Control Preference Scale (CPS) is the most frequently used instrument to assess patient preferences for involvement in decisions about their health [Degner 2007; Kryworuchko 2008]. It consists of five “cards” on a board, each illustrating a different role in decision-making by means of a cartoon and short descriptive statement. In its original version, administration requires a trained examiner, who asks the patient to choose the preferred card, which is then covered up. The procedure continues (four choices) until one card is left. If the second preference is incongruent with the first (non- adjacent pairing, such as card A with card C), the test is explained again, and immediately re-administered. In the event of a further incongruence, the test is not re-administered, and a preference is not assigned. Six scores are possible based on the subject's two most preferred roles: active–active, active–collaborative, collaborative–active, collaborative–passive, passive–collaborative, and passive–passive. These scores are grouped as: active (active–active or active–collaborative), collaborative (collaborative–active or collaborative–passive), or

passive (passive–collaborative or passive–passive) [Degner 2007]. We will use the electronic Italian self-administered CPS (eCPS) [Solari 2013].

#### **5.3.4 Quality of the ACP conversation**

*OPTION scale* - Structured observations of audio recorded ACP conversations will be assessed using the OPTION scale. The ACP conversation will be unobtrusively audio-taped and transcribed verbatim; subsequently it will be rated by a specially trained third observer using the Observing Patient Involvement in Shared Decision Making (OPTION) scale. OPTION (<http://www.glynelwyn.com/observer-option-instrument.html>) is an observer-based scale that evaluates the behavior of the physician in terms of patient involvement in decision-making [Elwyn 2005]. It consists of 12 items, each rated on a five-point Likert scale ranging from 0 (behavior not observed) to 4 (behavior observed to high standard). A total score (range 0–48) is obtained by adding the scores of each item. OPTION has been validated in seven languages, including Italian [Goss 2007].

*QOC, QOC-SO and QOC-Doc* - After the ACP conversation, pwPMS will complete the Quality of Communication Questionnaire (QOC) [Engelberg 2006]; SOs will complete the SO version, and physicians the physician version (last two items) of the QOC. Developed from qualitative studies with patients, families, and clinicians, the QOC consists of 19 items measuring general communication (ten items) and communication about EOL care (nine items), each rated on a scale from 0 ('very worst I can imagine'/'not at all') to 10 ('very best I can imagine'/'extremely'), or identified as something the clinician did not do. The 0/10 ratings are recoded to 1/11, with 0 imputed for 'did not do' (<http://depts.washington.edu/eolcare/products/instruments/>). A SO's version of the inventory (QOC-SO), and a physician's version (QOC-Doc, made of the last two items only) will be also devised for this study.

#### **5.3.5 Quality of life**

The 29-item Multiple Sclerosis Quality of Life (MSQOL-29) is the shortened form of the MSQOL-54 [Rosato 2016; Rosato 2019], one of the most used HRQOL inventories in MS. It includes 25 items forming 7 subscales and 4 single items, and one filter question for 3 'sexual function' items. We will use the electronic version (eMSQOL-29) of the questionnaire [Rosato 2019].

#### **5.3.6 Caregiver burden**

The Zarit Burden Interview (ZBI) [Hérbert 2000] is a 22-item self-report measure of subjective burden among caregivers. It addresses functional and behavioral impairments as well as the home care circumstances. Items are scored on a 5-point Likert scale ranging from 0 (never) to 4 (nearly always present). A total 0 (low burden) to 88 (high burden) score is obtained by summing item responses. We will use the Italian ZBI version [Chattat 2010].

